### Statistical analysis

The test data will be analyzed by a statistical expert using SPSS version 22.0 (Chicago, IL, USA). The statistical expert is not involved in the experiment and is only responsible for the analysis of the data. We will use descriptive statistical methods to measure demographics and baseline clinical features. The difference in the primary outcome between the two groups will be examined using the *t test.* A rank sum test will be used to compare the satisfaction with pain relief between the two groups. A chi-square test will be used to analyze the patients’ acceptance of analgesia. Adverse effects will be tested by the chi-square test. Physiological parameters will be compared using the repeated measures analysis of variance. Besides the complete case analyses, multiple computations are used to replace the missing values in the resulting parameters. Data will be performed with an intention-to-treat analysis. All results are statistically significant with *p* < 0.05.

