#### Inclusion criteria

Patients who meet the following inclusion criteria will be enrolled in the trial:
The patient met the Chinese PHN clinical diagnostic criteria (PHN is defined as pain persisting for ≥ 1 month after HZ rash healing [37]);Over the age of 18;Pain score ≥ 4 according to the Numerical Rating Scale (NRS); andVolunteered to participate and signed the informed consent.

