### Measurement

We will use a form to collect the baseline characteristics of patients, including age, gender, weight, height, education level, employment status, medical burden (no burden at all, basically no burden, some burden, heavy burden), location of pain, and course of the disease. Besides, the patients’ pain intensity, physiological parameters (blood pressure, heart rate, percutaneous oxygen saturation), patients’ acceptance of the analgesia, patients’ satisfaction with pain relief, and adverse effects will be recorded.

NRS will be used to assess the intensity of pain, ranging from 0 to 10, where 0 means “painless” and 10 means “worst pain imaginable” [38]. In most cases, clinicians and patients tend to use NRS to assess pain levels. Patients choose a number to represent their pain degree according to their feelings, which is easy to be understood by patients, is easy to use, and even can obtain scores in oral use, with high reliability and validity [39]. The reliability of the NRS has been proven to be moderate to high, with a maximum of 0.96. Besides, the convergence validity of NRS is 0.79 to 0.95 [40]. The patients’ physiological parameters will be monitored with an electronic sphygmomanometer (OMRON, HEM-7120) and oximeter (PC-60B). Pain intensity and the physiological parameters will be monitored simultaneously at baseline (T0), 5 min (T1), and 15 min (T2) after the trial began and at 5 min (T3) after the trial ended. Patients’ satisfaction with pain relief will be measured by a 5-point Likert scale (5, very satisfied; 4, satisfied; 3, uncertain; 2, dissatisfied; 1, very dissatisfied) [41]. The 5-point Likert scale is one of the Likert scales. Likert scale plays an important role in psychological research, which is the main method to measure attitude and personality. Besides, the Likert scale is easy to implement [42]. Furthermore, the data collectors will inquire into the patient’s acceptance of analgesia by asking the patient whether they would accept the gas inhalation to ease the pain (yes/no). Satisfaction and acceptance will be investigated at T3.

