### Outcome measure

#### Primary outcome measure

The primary outcome measure is pain intensity, which will be measured by NRS. The data collector will assess pain intensity at baseline, T1, T2, and T3. Before trial, patients will be taught to use the NRS to assess the pain intensity by pointing out the appropriate number (range = 0 to 10), without having to take off the facemask, thus ensuring continued inhalation of the gas.

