### Sample size calculation

We performed a pilot trial to calculate the sample size. According to our previous study on breakthrough pain [44], the sample size is calculated based on the pain intensity of patients, because the pain intensity is a primary outcome measure. Ducassé et al. [43] conducted a study on the analgesic effects of pre-mixed nitrous oxide and oxygen on patients with out-of-hospital trauma. The study confirmed that pain intensity in the intervention group (nitrous oxide/oxygen mixture) was significantly lower than that in the control group (medical air) at 5 min after administration (*p* < 0.001). Therefore, we used the pain intensity recorded at T1 as a reference in calculating the sample size. Our pilot trial involved 14 patients, with a 1:1 ratio between the intervention group and the control group. The sample size of this study was calculated by the following formula:

$$ {n}_1={n}_2=2{\left[\frac{\left({u}_{\alpha }+{u}_{\beta}\right)}{\raisebox{1ex}{$\delta $}\!\left/ \!\raisebox{-1ex}{$\sigma $}\right.}\right]}^2+\frac{1}{4}{u}_{\alpha}^2 $$where *n*_1_ and *n*_2_ represent the sample sizes of each group. ***δ*** is the difference value between the two population means. ***σ*** represents the population standard deviation. According to the pilot trial, the pain severity during the test reported by all control group patients (*n* = 7) revealed a mean (SD) of 6.71 (1.28) out of 10. Patients (*n* = 7) in the intervention group reported a mean (SD) of 4.50 (1.80). So we got *δ* = |*μ*_1_ − *μ*_2_| =2.21. The standard deviation of the entire sample (*n* = 14) was 1.93, which was ***σ*** =1.93. ***α*** represents a significance level of 5% for a two-sided test, ***u***_***α***_ = 1.96. ***β*** was the type II error, which was set to 0.1; thus, ***u***_***β***_ = 1.282. We substituted these data into the formula and calculated that *n*_1_ and *n*_2_ were 16.9. Therefore, the sample size of each group was about 17. Taking into account the 20% drop-out rate before the end of the study, we decided to enroll a total of 42 participants (21 per group).

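### The primary t test names no baseline covariate although T0 pain is recorded in every patient: valid, but it gives up precision and leaves chance baseline imbalance uncorrected

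*Protocol article*

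**What the plan says.** The Statistical analysis section fixes the method for the primary outcome: "The difference in the primary outcome between the two groups will be examined using the" t test. No covariate is mentioned. The only role it gives to baseline data is descriptive: "We will use descriptive statistical methods to measure demographics and baseline clinical features". Repeated measures analysis of variance is planned, but only for the physiological parameters.

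Under Primary outcome measure the article states "The primary outcome measure is pain intensity, which will be measured by NRS" and "The data collector will assess pain intensity at baseline, T1, T2, and T3". The Measurement section gives the same schedule, so a baseline value of the primary outcome is planned for every participant. Inclusion criteria set a floor for it: "Pain score ≥ 4 according to the Numerical Rating Scale (NRS").

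The Sample size calculation section says "we used the pain intensity recorded at T1 as a reference in calculating the sample size". It then uses the pilot means 6.71 and 4.50 and a raw-score SD of 1.93. The randomisation section describes a computer-generated 1:1 list and states no stratification by baseline pain.

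**The concern.** T0 pain is scored on the same scale as T1 pain, and T1 comes only 5 minutes after inhalation starts. T0 is therefore a natural predictor of T1 pain. As described, neither the allocation nor the primary analysis uses it.

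Two things are at stake. One is precision: variation in T1 pain that T0 could explain stays in the error term, so the confidence interval is wider than it needs to be. The other is chance imbalance: in a trial of 42, the arms may start at noticeably different pain levels, and an unadjusted comparison carries part of that difference into the estimated effect of the gas. Both can be addressed with data already planned.

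**Working it through.** **Inputs from the Sample size calculation section.** Difference δ = 2.21, SD σ = 1.93, two-sided α = 0.05 (1.96), β = 0.1 (1.282), 17 evaluable and 21 enrolled per group. Pilot arm SDs are 1.28 and 1.80, with 7 patients per arm.

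**Inputs assumed, because the article does not give them.** T0–T1 correlation r = 0.3 to 0.6; baseline SD 1.5 (range 1.28 to 1.93).

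**1. The plan's own figure.** n = 2[(1.96 + 1.282)/(2.21/1.93)]² + 1.96²/4 = 16.03 + 0.96 = 16.99 per group. The article gives 16.9 and rounds to 17, so the figure reproduces. The inputs are raw T1 scores with no allowance for baseline.

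**2. Precision.** ANCOVA multiplies the residual variance by 1 − r². The equivalent increase in sample size is 1/(1 − r²).

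| r | variance factor | reduction | residual SD (1.93 × √(1 − r²)) | equivalent n |
|---|---|---|---|---|
| 0.3 | 0.91 | 9% | 1.84 | × 1.10 |
| 0.5 | 0.75 | 25% | 1.67 | × 1.33 |
| 0.6 | 0.64 | 36% | 1.54 | × 1.56 |

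**3. Power.** Noncentral t with noncentrality δ/(SD × √(2/n)). Degrees of freedom are 2n − 2 for the t test and 2n − 3 for ANCOVA.

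| Scenario | t test | r = 0.3 | r = 0.5 | r = 0.6 |
|---|---|---|---|---|
| Protocol inputs (2.21, 1.93), 17 per group | 90% | 92% | 96% | 98% |
| Protocol inputs, 21 per group | 95% | 97% | 99% | 99% |
| Assumed difference 1.5, SD 1.56, 17 per group | 78% | 81% | 88% | 92% |

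The SD of 1.56 is the pooled within-arm pilot value, √((1.28² + 1.80²)/2). The difference of 1.5 is not in the article; it illustrates an effect smaller than planned. It lies well inside the pilot's uncertainty: the standard error is 1.56 × √(2/7) = 0.83, and 2.21 ± 2.18 × 0.83 runs from about 0.4 to 4.0.

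**4. Chance imbalance at T0.** The standard error of the baseline difference is SD × √(2/n). With SD 1.5 and 21 per group it is 0.46, so the 95% range is ±1.96 × 0.46 = ±0.91 points. With SD 1.28 to 1.93 the range is ±0.77 to ±1.17. With 17 per group and SD 1.5 it is ±1.01.

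The share passed into an unadjusted estimate is the regression slope of T1 on T0. If the SDs at T0 and T1 are equal, the slope equals r. An imbalance of 0.91 would then shift the estimate by 0.91 × 0.3 = 0.27 to 0.91 × 0.6 = 0.55 points, or 12% to 25% of the planned 2.21.

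**The case against.** The strongest counter-argument is that nothing here is an error. Under 1:1 randomisation the unadjusted t test is unbiased over repeated allocations and keeps its type I error. It also agrees with the sizing on raw T1 scores. That stands. A reader might infer from the missing covariate that the primary test is invalid or the trial's result biased; the documents do not support that. The bias at issue is conditional on a particular imbalance.

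A second stronger reading is that the plan expressly ignores T0. The text does not say so. It does not state whether the t test is on raw scores or on change, and baseline is listed among the primary-outcome assessments. The T1 sizing makes raw scores the likely reading, not a certain one. An analysis of change would use T0, but with the slope forced to 1. With equal SDs, the change score has variance 2(1 − r) times that of the raw score, so it is less precise when r is below 0.5.

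Third, the power benefit is easily overstated. A rise from 78% to 92% depends on an assumed difference of 1.5. On the protocol's 2.21 and 1.93 the gain is about 2 to 8 percentage points from a base of 90%, and smaller still if all 21 per group are evaluable. This also stands.

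Fourth, r and the baseline SD are unknown, and the entry floor of NRS 4 narrows the baseline range and may lower r. At r = 0.3 the variance saving is only 9%.

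The silence is not simply detail left to a separate analysis plan: the article names the test, so this is a stated choice.

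**Conclusion.** The point holds as an improvement in efficiency and robustness to a valid test. The direction of the gain is secure for any appreciable T0–T1 correlation; its size is not, because the article reports neither that correlation nor the baseline SD. The reduction in variance and the exposure to imbalance are the main reasons to change. The power gain is modest if the planned effect is real, and it becomes material only if the true effect is smaller than planned.

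**What to change.** In the Statistical analysis section, replace the t test for the primary outcome with ANCOVA: NRS at T1, the time point used for sizing, on treatment group with T0 NRS as covariate. Report the adjusted mean difference with its 95% CI, and keep the unadjusted t test as a sensitivity analysis.

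The cost is a change of wording and one degree of freedom. No new data or extra patients are needed. The article reports 20 of 42 participants recruited and gives researchers access to the data for analysis only on completion, so on that timetable the change could be fixed before results are known.

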## Methods/design

### Aim

The main aim of the study is to evaluate the analgesic effect of the fixed nitrous oxide/oxygen mixture on patients with PHN. There are three secondary aims of the study:
To evaluate the safety of the fixed nitrous oxide/oxygen mixture by monitoring patients’ physiological parameters and adverse effectsTo determine the satisfaction of patients with the analgesic effect of the fixed nitrous oxide/oxygen mixtureTo investigate the acceptance of patients to the fixed nitrous oxide/oxygen mixture analgesia

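### A chi-square p-value is the only analysis named for adverse effects, and with 21 patients per arm it cannot by itself answer the safety aim

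*Protocol article*

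**What the plan says.** The Aim section lists safety first among three secondary aims: "To evaluate the safety of the fixed nitrous oxide/oxygen mixture by monitoring" physiological parameters and adverse effects. For the adverse effects, the Statistical analysis section names one method: "Adverse effects will be tested by the chi-square test". The same test is assigned to acceptance ("A chi-square test will be used to analyze the" patients' acceptance of analgesia). One rule then covers every outcome: "All results are statistically significant with" p < 0.05. The article does not say whether the chi-square test is continuity-corrected, or whether it is run per type of adverse effect or on any adverse effect.

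The Sample size calculation section fixes 21 per group from pain at 5 minutes only. The Measurement section lists seven expected adverse effects (nausea, vomiting, dizziness, drowsiness, headache, hypotension, oxygen desaturation). The Background calls adverse reactions uncommon. No rate is given anywhere.

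**The concern.** A small trial, uncommon events and a bare p-value fit together poorly. Two things follow.

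- In sparse tables the verdict can depend on which version of the chi-square test is run, and the plan does not fix this. The choice could then be made after the data are seen.
- A test with little power usually returns a non-significant result even when there is a real excess of harm. The p-value on its own therefore carries little information on the aim it is meant to serve.

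The Discussion proposes the gas as an emergency therapy that could reduce opioid use, so what the trial can say about safety matters.

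**Working it through.** **Inputs from the article.** Allocation is 1:1. The sample size uses alpha ("represents a significance level of 5% for a two-sided test") and beta ("was the type II error, which was set to 0.1"). The pilot control group "revealed a mean (SD) of 6.71 (1.28) out of 10", and patients "in the intervention group reported a mean (SD) of 4.50 (1.80"), so the difference is 6.71 − 4.50 = 2.21; the SD used is 1.93.

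**The plan's own figure.** n = 2[(1.96 + 1.282)/(2.21/1.93)]² + 1.96²/4 = 16.03 + 0.96 = 16.99 per group. The article gives 16.9 and uses 17. Then 17 × 1.2 = 20.4, hence 21 per group and 42 in total. The figure reproduces, and adverse effects play no part in it.

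**When tables are sparse.** With equal arms, the expected number of events per arm is half the total. It is below 5 when fewer than 10 of 42 patients (10/42 = 23.8%) have the event. The event rates below are assumptions. Each probability is a sum over all pairs of binomial counts at 21 per arm.

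| Rate, both arms | Probability of an expected count below 5 | True size, uncorrected chi-square |
|---|---|---|
| 5% | over 99% | 1.3% |
| 10% | 99% | 4.1% |
| 15% | 91% | 5.1% |
| 20% | 68% | 5.2% |
| 25% | 37% | 5.4% |
| 30% | 15% | 5.6% (the maximum) |

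Sparse tables are thus close to certain for an individual effect at rates up to about 15%. They are not certain for a composite or for a common effect.

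**Which chi-square.** For 4/21 v 0/21:
- Uncorrected: 42 × (4×21 − 0×17)² / (21×21×4×38) = 42 × 84²/67,032 = 4.42, p = 0.035.
- Continuity-corrected: 42 × (84 − 21)²/67,032 = 2.49, p = 0.115.

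Two other tables with fewer than 10 events also split: 5 v 0 (0.017 v 0.057) and 6 v 1 (0.038 v 0.098).

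**Exact tests in the two tables where uncorrected chi-square and Fisher disagree (fewer than 10 events).** Enumeration with the group sizes fixed gives:

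| Table | Uncorrected | Fisher | Barnard | Boschloo |
|---|---|---|---|---|
| 4 v 0 | 0.035 | 0.107 | 0.044 | 0.056 |
| 6 v 1 | 0.038 | 0.093 | 0.0497 | 0.048 |

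**Power at 21 per arm, two-sided 5%.**

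| Assumed rates | Uncorrected chi-square | Fisher |
|---|---|---|
| 10% v 1% | 13% | 4% |
| 20% v 5% | 31% | 19% |
| 20% v 2% | 48% | 30% |
| 30% v 5% | 62% | 48% |

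**What an interval shows.** For 2/21 v 0/21 the uncorrected statistic is 42 × 42²/(21×21×2×40) = 2.10, p = 0.15. The Wilson limits are 2.7% to 28.9% for 2/21 and 0 to 15.5% for 0/21. The Newcombe interval for the difference of 9.5 points is:
- lower: 0.0952 − √[(0.0952 − 0.0265)² + 0.1546²] = −0.074
- upper: 0.0952 + (0.2891 − 0.0952) = 0.289

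That is −7 to +29 points. With no events in 21 patients, the exact two-sided upper limit for the rate is 1 − 0.025^(1/21) = 16.1%.

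**The case against.** The strongest reply is that the planned test is sound. Its true size at 21 per arm never exceeds 5.6% and is far below 5% for rare events. Disagreement with Fisher's test does not convict it, because Fisher is conservative (true size at most about 2.4%) and is less able to detect harm: 30% power against 48% at 20% v 2%. Barnard's unconditional test agrees with uncorrected chi-square in both discordant tables. All of this stands. A reader might infer that sparse tables make the chi-square test invalid, or that Fisher's test is required; the figures support neither.

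A reader might also infer that the plan will take p > 0.05 as proof of safety. No section says so. The safety aim also draws on physiological parameters, and every adverse effect is to be observed and recorded.

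It is also fair that the low power comes from having 42 patients and that no choice of test removes it. Further, the event rates are assumed, and a composite of any adverse effect, or acceptance, may be common enough for expected counts to reach 5. At 50% v 10%, only 12% of trials have an expected count below 5.

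Finally, a full analysis plan that is not shown may add intervals or specify the test. That limits the point to what the article fixes: a named test, with its version unspecified, and one p-value rule for a stated aim.

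**Conclusion.** The point holds as a recommended improvement, not as an error that invalidates the analysis. The one method named for adverse effects rarely informs the safety aim: power is about 13% at 10% v 1%, 31% at 20% v 5% and 48% at 20% v 2%. A non-significant result is thus the likelier outcome even with a true excess of 15 to 18 points. In borderline tables the unspecified continuity correction can reverse the verdict (0.035 v 0.115 for 4 v 0).

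The sparse-table statement rests on assumed rates of up to about 15% in both arms and applies to individual adverse effects. The false-positive rate is not materially inflated. The primary analysis and the sample size are unaffected.

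**What to change.** Amend the Statistical analysis section so that each adverse effect, and any adverse effect, is reported as counts per arm and a risk difference with a 95% Newcombe or score interval. State that the conclusion on safety rests on that interval and not on p > 0.05. If a p-value is kept, name one test in advance: either uncorrected chi-square or one specified unconditional exact test. The unconditional test must be named individually, because for 4 v 0 Barnard (0.044) and Boschloo (0.056) fall on opposite sides of 0.05.

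This needs a sentence or two of wording and no extra patients or data. Recruitment stood at 20 when the article was submitted, so the wording could still be settled before analysis. The cost is slightly more reporting, and wide intervals that will make the safety statement more modest.

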### Interventions

A clinician is responsible for assessing the patient’s condition on the ward, determining whether the patient meets the inclusion criteria, and informing the patient of the purpose of the trial, methods, possible risks, and rights of participants. Patients who meet the inclusion criteria will sign an informed consent form after agreeing to participate in the trial. The project manager will group patients who agree to participate in the trial based on the randomly assigned list and escort the patient to the treatment room, where the trial will be conducted. All patients in the trial will receive routine treatment (oral pregabalin 75 mg twice daily). Patients in the intervention group will inhale nitrous oxide/oxygen mixture with a facemask, which is a visible intervention measure. To eliminate the influence of psychological factors on the experimental results of patients in the control group, patients in the control group will inhale oxygen by a facemask. Patients in the intervention group will receive routine treatment plus a fixed nitrous oxide/oxygen mixture (contains 65% nitrous oxide and 35% oxygen), while patients in the control group will receive routine treatment plus oxygen. Before inhaling the gas, the data collector will teach the patient to use the NRS to report pain intensity. Besides, the data collector will inform patients that they have the right to stop or quit the trial at any time if they experience discomfort during the study. Before the trial begins (T0), the data collector will record the patient’s demographic and baseline characteristics; assess the patient’s pain intensity; measure heart rate, blood pressure, and percutaneous oxygen saturation; and teach the patient to inhale gas using a facemask. Patients in both groups will inhale gas using an oral-nasal mask, which is disposable and has a one-way valve. According to our previous research, the gas intake will last for 15 min [33, 34]. When the data collector opens the valve of the cylinder and the patient puts on the mask to inhale the gas, the trial will start timing. The data collector will assess the patient’s pain intensity and measure blood pressure, heart rate, and percutaneous oxygen saturation at the beginning of the trial at 5 min (T1) and 15 min (T2). To assess the patient’s pain, the data collector will ask the patient: How bad is the pain now? Patients will point to the corresponding pain score with their fingers and without having to remove the facemask. Five minutes after the end of the trial (T3), in addition to collecting the data mentioned above, the data collector will ask patients about their satisfaction with pain relief and acceptance of analgesic methods. Throughout the trial, the data collector will closely observe and ask the patient whether there are adverse effects.

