Starting with gas inhalation, the data collectors will carefully observe and record any adverse effects on the patient. The expected adverse effects of nitrous oxide/oxygen mixture therapy include nausea, vomiting, dizziness, drowsiness, headache, hypotension, and oxygen desaturation [29]. If any adverse effects occur, the study will be terminated immediately, the patient will be given oxygen, and the adverse effects will be fully reversible in 5 min [43]. Any adverse effects concerning the intervention will be recorded throughout the trial period.

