#### Secondary outcome measures

The following are the secondary outcomes:
Patients’ satisfaction with pain reliefPatients’ acceptance of analgesiaAdverse effectsPhysiological parameters (blood pressure, heart rate, percutaneous oxygen saturation)

Data collectors will collect data on patients’ satisfaction with pain relief, patients’ acceptance of analgesia, and adverse effects at T3. Patients’ physiological parameters will be collected at baseline, T1, T2, and T3 (Fig. 2).

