**Fig. 2 Fig2:**
[figure not shown]
SPIRIT figure: schedule of enrolment, interventions, and assessments. PHN postherpetic neuralgia, T0 baseline, T1 5 min after starting the therapy, T2 15 min after starting the therapy, T3 5 min after finishing the therapy

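### The repeated measures ANOVA planned for heart rate, blood pressure and SpO2 states no adjustment for the pre-gas T0 reading; a T0-adjusted analysis of T1 to T3 is more efficient and needs no new data

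*Protocol article*

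**What the plan says.** In the protocol article, the Statistical analysis section gives these variables one sentence: "Physiological parameters will be compared using the repeated measures analysis of variance". It names no covariate, no change score and no particular effect to be read.

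The Secondary outcome measures section gives the schedule: "physiological parameters will be collected at baseline, T1, T2, and T3". T0 is before gas, as the Interventions section shows: "Before the trial begins (T0), the data collector will record the patient". T3 is after gas; the legend of Fig. 2 defines it as "T3 5 min after finishing the therapy".

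These readings serve the first secondary aim, which begins "To evaluate the safety of the fixed nitrous oxide/oxygen mixture by monitoring patients". On early stopping, the Measurement section says: "If any adverse effects occur, the study will be terminated immediately". The Statistical analysis section plans complete-case analyses, replacement of missing values, and analysis by intention to treat.

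**The concern.** Randomisation makes the expected group difference at T0 zero, so T0 carries no treatment effect. It is still the best available predictor of each patient's later readings. A four-level ANOVA of group by time does not use it in that way.

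- **Group main effect.** This averages the four times. One of them has no true difference, and stable differences between patients stay in the error term.
- **Group-by-time interaction.** Here T0 supplies the contrast and nothing is diluted. But the test in effect subtracts T0 in full instead of weighting it by its correlation with the later readings, and that costs efficiency.

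A test with low power tends to return no significant difference, and in a safety comparison that can be read as reassurance.

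A smaller point concerns missing readings. Classical repeated measures ANOVA needs every level. A patient whose session ends because of hypotension or desaturation may lack a later reading, and would then fall out of the complete-case version.

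**Working it through.** **What the document gives.** The Sample size calculation section has "represents a significance level of 5% for a two-sided test" and "was the type II error, which was set to 0.1", for pain at T1 only. Its formula reproduces: 2 × [3.242/(2.21/1.93)]² + 1.96²/4 = 16.99, so 17 per arm. With the dropout allowance, 17 × 1.2 = 20.4, so 21 per arm. No effect size, SD, correlation or power is given for the physiological parameters, so there is no planned figure to reproduce for them.

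**Assumptions.**
- n = 21 per arm, two-sided 5%, equal variances.
- Equal correlation r between any two readings; sphericity for the interaction.
- No true difference at T0. The difference after T0 is 0.7 SD, either at T1, T2 and T3 (constant) or at T1 and T2 only (gone by T3).

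**Formulas.** Let δ be the differences at T1 to T3 in SD units, A = Σδ and B = Σδ².

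1. Main effect over four levels: noncentral t, 40 df, ncp = (A/4) / √((1+3r)/4) × √(n/2).
2. Interaction with T0 as a level: noncentral F, 3 and 120 df, λ = (n/2)/(1−r) × [B − A²/4].
3. T0-adjusted joint test over T1 to T3: noncentral F, 3 and 37 df (a cautious choice), λ = (n/2)/(1−r) × [B − rA²/(1+3r)].
4. T0-adjusted mean of T1 to T3: noncentral t, 39 df, ncp = (A/3) / √((1+2r)/3 − r²) × √(n/2).

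**Numbers at r = 0.5, constant effect.** A = 2.1 and B = 1.47.

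1. Main effect: the averaged difference is 2.1/4 = 0.525 SD, three quarters of 0.7. ncp = 0.525/0.791 × 3.240 = 2.15; power 56%.
2. Interaction: λ = 21 × (1.47 − 1.1025) = 7.72; power 62%.
3. Joint T0-adjusted test: λ = 21 × (1.47 − 0.882) = 12.35; power 81%.
4. T0-adjusted mean: ncp = 0.7/0.645 × 3.240 = 3.51; power 93%.

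**Numbers at r = 0.5, gone by T3.** A = 1.4 and B = 0.98.

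- Interaction: λ = 21 × (0.98 − 0.49) = 10.29; power 76%.
- Joint T0-adjusted test: λ = 21 × (0.98 − 0.392) = 12.35; power 81%.
- T0-adjusted mean: ncp = 2.34; power 63%.

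**Range over r (power, %).**

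| Effect | r | Main effect | Interaction | Joint, T0-adjusted | T1–T3 mean, T0-adjusted |
|---|---|---|---|---|---|
| Constant | 0.3 | 67 | 47 | 78 | 91 |
| Constant | 0.5 | 56 | 62 | 81 | 93 |
| Constant | 0.7 | 47 | 85 | 92 | 98 |
| Constant | 0.8 | 44 | 97 | 98 | >99 |
| Gone by T3 | 0.3 | 36 | 60 | 71 | 60 |
| Gone by T3 | 0.5 | 29 | 76 | 81 | 63 |
| Gone by T3 | 0.7 | 24 | 94 | 95 | 75 |
| Gone by T3 | 0.8 | 22 | 99 | 99 | 87 |

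**Why the joint test is the like-for-like comparison.** Lines 2 and 3 both have 3 numerator df and differ only in the multiplier of A²: 1/4 against r/(1+3r). The second is smaller whenever r is below 1, because 4r < 1 + 3r. So under equal correlation the T0-adjusted noncentrality is never the lower one, whatever the pattern over time. The two meet as r approaches 1, which is why the gain fades at high correlation.

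**Missing readings, invented illustration.** Suppose 4 of 21 patients on the mixture stop after a 20 mmHg fall and lack a later reading, and 17 fall by 3 mmHg. The complete-case mean fall is 3.0 mmHg; over all 21 it is (17 × 3 + 4 × 20)/21 = 6.2 mmHg.

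**The case against.** The strongest reply is that the article does not commit to the analysis criticised. It names a method and, elsewhere, a collection schedule. It does not say that T0 is an outcome level or that the group main effect is the test read. An article may leave such detail to a fuller document. A reader might infer that the plan dilutes the safety effect by a quarter. The text does not support that as a fact: it needs T0 as a level, the main effect as the test, and a constant effect over T1 to T3. This part of the reply stands, and the dilution is therefore conditional.

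Second, a constant effect is open to doubt. T3 is after the gas has ended, and the article itself describes quick recovery. If the effect has gone by T3, the interaction (76% at r = 0.5) beats the T0-adjusted mean (63%). That is correct, and the T1 to T3 mean should not be the only summary. But it sets a 3-df test against a 1-df mean. The T0-adjusted joint test does not lose that comparison (81%).

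Third, a reader might infer that every patient who stops early is lost, or that the analysis is biased towards finding no difference. Neither follows. Missing values are also to be replaced and the analysis is by intention to treat, so the loss concerns the complete-case version. Adverse effects are compared separately by chi-square test. The Interventions section lets the data collector judge whether a session continues, whereas the Measurement section ends it. Those passages need reconciling, and until they are, the frequency of early stopping is unknown. Without dropped patients, the issue is lower power, not bias in the test.

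**Conclusion.** The point holds as an efficiency finding. The plan states no T0 adjustment, and under either reading of a four-level ANOVA a more efficient analysis of the same data exists. At 0.7 SD, correlation 0.5 and 21 per arm, a constant effect is detected with 56% power (main effect) or 62% (interaction), against 81% to 93% with T0 adjustment. The advantage over the interaction narrows to 81% against 76% if the effect has gone by T3, and is small at correlation 0.8 or more. All these figures rest on an assumed effect size and correlation, because the document gives neither for these variables. They are secondary safety measures for which no power was claimed. The sample size and the primary analysis are untouched.

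**What to change.** Replace the sentence in the Statistical analysis section with wording such as: each physiological parameter at T1, T2 and T3 will be analysed with a linear mixed model with the T0 value as covariate and group, time and group-by-time as fixed effects, using all available readings. The group effect will be tested jointly over T1 to T3, and the adjusted group difference with its 95% confidence interval will be reported at each time.

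The joint test covers both a constant effect and one that has gone by T3. The estimates at each time show the size of any change, which a safety reader needs more than a p-value. The model keeps a patient who has some but not all of the later readings. It does not recover a patient with none, so the planned imputation and the separate adverse-effect comparison should stay.

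The cost is a change of analysis wording. T0 is already collected, and no new patients, visits or measurements are needed. If T0 adjustment is already intended, stating it is enough.
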